### **6. Interim analysis and stopping criteria**

Based on the research ethics, the interim analysis will be done between 10 to 20 months after the recruitment; if there is a beneficial prognostic trend, the trial will continue, otherwise it will be terminated.

This research has entrusted Taiwan Clinical Trial Bioinformatics and Statistical Center (which is founded by National Research Program for Biopharmaceuticals at the Ministry of Science and Technology of Taiwan) to provide interim analysis and final analysis assistance.

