### **5. Sample size estimation**

The sample size estimation is based on the primary outcome of sustained ROSC. According to previous study conducted in Taipei, sustained ROSC rate was 24.4% for SGA and 30.8 % for ETI. [15]

We estimated to enroll 852 patients to detect the absolute difference of 6.4% between the SGA and ETI group to have 80% power and a two-sided  $\alpha$ -level of 0.05.

Considering the number of OHCA patients treated by the participating ALS teams in Taipei is about 300 patients annually, we expect to have adequate number of patients of the three years study period.

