### **8.2. Year 2**

- Call regular expert meetings to follow the progress of the trial
- Regularly report to the Institutional review board
- Regularly analyze and improve the compliance of the participating paramedics
- Conduct the first-time interim analysis

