### **8.3. Year 3**

- Call regular expert meetings to follow the progress of the research and disclose the final research results
- Conduct the second-time interim analysis
- Complete allocation and also start preliminary data analysis

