## **9. Analytic plan**

The statistical analysis methods include descriptive analysis, T-test, Chi-squared test, logistic regression, and propensity score analysis.

For the effect of airway management devices between ETI and SGA, odds ratios and 95% confidence intervals will be calculated. All tests are two-sided, and a p-value  $< 0.05$ , will be considered statistically significant.

The analysis will be done according to both intention-to-treat and as-treated principles, and reported according to the CONSORT guidelines.

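### The interim rule in Section 6 makes termination the default without defining the trend that avoids it, and Sections 6 and 8 disagree on the number of looks

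*Protocol*

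**What the plan says.** Section 6 (Interim analysis and stopping criteria) speaks of a single analysis: "the interim analysis will be done between 10 to 20 months after the recruitment". Its decision rule is "if there is a beneficial prognostic trend, the trial will continue, otherwise it will be terminated". It does not say which outcome is examined, which arm must be ahead, by which statistic, or by how much.

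The timeline has two analyses. Section 8.2 (Year 2) lists "Conduct the first-time interim analysis" and Section 8.3 (Year 3) lists "Conduct the second-time interim analysis".

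Section 9 states "All tests are two-sided" at the 0.05 level. Section 5 sizes the trial at 852 patients to "detect the absolute difference of 6.4% between the SGA and ETI group to have 80% power and a two-sided" α of 0.05, on the basis that "sustained ROSC rate was 24.4% for SGA and 30.8 % for ETI". Section 4.1 hypothesises that ETI is better, Section 4.6.1 makes ETI the intervention, and Section 2 gives the wider aim of finding the best prehospital airway strategy.

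**The concern.** This is a written, mandatory rule, not a detail left open. Unless the undefined trend appears, the trial ends, and an SAP could not soften that without contradicting the protocol.

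The paramedics are already authorised to use both airways (Sections 3 and 4.4), so a result favouring SGA, or a precise neutral result, would also inform practice. If the trend means ETI ahead, the rule works in one direction only, although the testing is declared two-sided. It can end the trial on a small, imprecise difference.

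Separately, one look and two looks give different stopping probabilities, so the protocol as it stands does not determine how the trial would behave.

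**Working it through.** **Number and timing of looks.** Section 6 has one analysis in recruitment months 10-20. Section 2 gives 34 months of enrolment within a three-year plan, so recruitment starts by about plan month 36 − 34 = 2. Year 3 opens at plan month 24, which is recruitment month 22 or later. A Year 3 look therefore appears to fall outside the window in Section 6.

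**The plan's own figure.** The interim rule states no error rate or stopping probability. The only related figure is the sample size. With 24.4% v 30.8%, 1:1, 80% power and two-sided 0.05, the pooled formula gives, per arm,

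[1.96·√(2·0.276·0.724) + 0.842·√(0.244·0.756 + 0.308·0.692)]² / 0.064² ≈ 765,

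that is 1,530 in total, not 852. This is a separate problem. It matters here because the comparison without the rule must use the actual power at 852:

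- SE = √[(0.244·0.756 + 0.308·0.692)/426] = 0.03055
- θ = 0.064/0.03055 = 2.095
- power = Φ(2.095 − 1.96) ≈ 55%

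**Inputs for the rule.** Accrual is about 300 a year (Section 5), or 25 a month, so months 10-20 give about 250-500 patients. The information fraction is t = months/34. Assumptions: the trial continues only if the observed sustained ROSC rate is higher with ETI (Z > 0); patients split 1:1, because Section 4.5 aims for balanced numbers; clustering is ignored.

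**Formulas, one look.**
- No true difference: P(stop) = Φ(0) = 50%.
- ETI +6.4 points: P(stop) = 1 − Φ(θ√t).
- SGA +6.4 points: P(stop) = Φ(θ√t).
- SGA significant at the stop, nominal 0.05: Φ(θ√t − 1.96).
- Trial completes and shows SGA better: bivariate normal probability that interim Z > 0 and final Z < −1.96, with correlation √t.
- 95% CI half-width: 1.96·√(2·0.276·0.724/n per arm).

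| | Month 10 | Month 15 | Month 20 |
|---|---|---|---|
| Patients | 251 | 376 | 501 |
| θ√t | 1.136 | 1.391 | 1.607 |
| Stop, no difference | 50% | 50% | 50% |
| CI half-width (points) | 11.1 | 9.0 | 7.8 |
| Stop, ETI +6.4 | 12.8% | 8.2% | 5.4% |
| Stop, SGA +6.4 | 87.2% | 91.8% | 94.6% |
| SGA significant at the stop | 20.5% | 28.5% | 36.2% |
| Completes and shows SGA better | 2.5% | 0.7% | 0.1% |
| Total chance of an SGA finding | 23.0% | 29.2% | 36.3% |

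At 426 per arm the half-width is 1.96·√(2·0.276·0.724/426) = 6.0 points.

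By symmetry, the power lost for ETI superiority equals the row for completed trials that show SGA better: at most about 2.5 points at one look.

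**Two looks, no difference.** P(stop) = 1 − [1/4 + arcsin√(t₁/t₂)/(2π)]. Months 20 and 30 give 59.8%, 15 and 24 give 60.5%, 10 and 24 give 63.8%, and 10 and 30 give 65.2%.

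**Sensitivity.** A simulation with patients split 60:40, counting ties as stops, gives 51% stopped under no difference, 13.7% / 8.9% / 6.0% with ETI better and 87.1% / 91.5% / 94.4% with SGA better (250 / 375 / 500 patients). With a total near 1,530 at the same look times, neutral trials still stop 50% of the time and SGA-better trials 94-98%. If the trend required one-sided p < 0.2, 80% of neutral trials would stop, as would 22-38% of those with the planned ETI benefit.

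**The case against.** The strongest reply is that Section 4.1 states a directional hypothesis, that a one-directional futility stop is a recognised choice which two-sided testing does not forbid, and that the rule costs ETI superiority little power. That stands, and it limits how serious the point is. It does not rescue a rule that makes termination mandatory without defining its trigger.

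A reader might infer more than the documents support:

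- *That the text itself stops the trial at any difference at or below zero.* It does not. Both the direction and the zero cut-off are inferred from Sections 4.1 and 4.6.1. If a trend towards either arm counts, the one-sidedness disappears.
- *That the trial could almost never show SGA better.* The 0.1-2.5% applies only to trials that run to completion. Nothing in the protocol bars testing the data at termination, and with such a test the chance is 23-36%.
- *That the rule destroys a conclusion of equivalence.* No equivalence test or margin is planned. With a half-width of 6.0 points at completion, excluding both +6.4 and −6.4 needs an observed difference within about 0.4 points of zero. That happens in roughly 10% of neutral trials: 2Φ(0.4/3.06) − 1.
- *That the interim looks inflate the false-positive rate.* The rule never stops for efficacy, so they do not.

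It is also fair to say that exact futility thresholds may be left to an SAP or interim charter.

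**Conclusion.** The point holds as a defect that should be fixed. Two parts need no assumption: the continuation criterion is undefined while termination is mandatory, and Sections 6 and 8 conflict on the number of looks. The second look's apparent place outside the Section 6 window rests on enrolment fitting within the three-year plan.

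The size of the harm depends on reading the trend as a higher observed sustained ROSC rate with ETI. On that reading, one look is a coin toss for a neutral trial and leaves an interval wider than the 6.4-point target difference on each side. It also ends most trials in which SGA is truly better, and lowers the chance of an SGA finding from about 55% to 23-36% without eliminating it. The cost to the ETI hypothesis is small and there is no alpha inflation. What is lost is information, in a trial declared two-sided and meant to find the best strategy.

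**What to change.** Amend the protocol in one paragraph:

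1. Make Sections 6 and 8 agree on the number and timing of looks, preferably at a fixed number of enrolled patients.
2. State that the interim decision uses sustained ROSC.
3. Replace automatic termination with a non-binding futility guide, met only when conditional power is low for a difference in either direction, for example below 10% under the planned 6.4 points. A symmetric extreme-evidence boundary is optional.

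The 10% is illustrative and depends on timing. Conditional power for a planned difference in either direction at interim Z = 0 is Φ[(θ(1 − t) − 1.96)/√(1 − t)]. For 852 patients this is 28% at month 10, 9.8% at 426 patients and 4.4% at month 20. The guide therefore cannot be met at month 10 and is barely reachable at 426 patients. At month 20 it is met when |Z| < 0.36, which is 2Φ(0.36) − 1 ≈ 28% of neutral trials. The threshold should be set together with the look, and revisited if the sample size is corrected.

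The cost is that some neutral trials run longer.

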### **7. Data collection:**

The data will be collected at the Utstein-style cardiac arrest registry system in Taipei, which consisted of the following items: patient demographics (age and sex); arrest characteristics (witness status, bystander CPR), locations (public or non-public), records on automated external defibrillator (shockable or non-shockable, chest compression fraction); out-of-hospital treatment, including airway types and medication used; patient records from the EMS receiving hospitals; patient outcomes (out-of-hospital return of spontaneous circulation, sustained return of spontaneous circulation [ $\geq 2$  hours], neurologic status at discharge), and time factors (response time, scene time, transport time, call to airway time [defined as the gap between the call of the dispatch center and advanced airway insertion completion]).

## **8. Timeline**

### **8.1. Year 1**

- Call expert meetings to achieve consensus on research
- Obtain Institutional review board approval of waiver of informed consent
- Prepare and start to allocation
- Establish relevant data collection for the trial

### **8.2. Year 2**

- Call regular expert meetings to follow the progress of the trial
- Regularly report to the Institutional review board
- Regularly analyze and improve the compliance of the participating paramedics
- Conduct the first-time interim analysis

### **8.3. Year 3**

- Call regular expert meetings to follow the progress of the research and disclose the final research results
- Conduct the second-time interim analysis
- Complete allocation and also start preliminary data analysis

## **9. Analytic plan**

The statistical analysis methods include descriptive analysis, T-test, Chi-squared test, logistic regression, and propensity score analysis.

For the effect of airway management devices between ETI and SGA, odds ratios and 95% confidence intervals will be calculated. All tests are two-sided, and a p-value  $< 0.05$ , will be considered statistically significant.

The analysis will be done according to both intention-to-treat and as-treated principles, and reported according to the CONSORT guidelines.

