#### **4. Trial Design**

This trial is a randomized controlled trial and will use cluster randomization with periodic crossover.

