#### **4.5. Randomization and blinding**

Four ALS teams will be divided into two randomization clusters. Each cluster is assigned to either ETI or SGA in a biweekly period. The study center will instruct the clusters to alternatively change to either the ETI or SGA according to the sequence random allocation.

To guarantee a balanced case number in the final analysis. The allocation periods of ETI vs. SGA in the fashion of three periods of ETI to two periods of SGA (3:2 ratio), which is based on the baseline first attempt success rates of ETI and SGA in the Taipei EMS system (i.e., the success rate of first attempt: 60% of ETI vs. 90% of SGA).

The blinding of paramedics is not possible due to the airway management devices cannot be concealed.

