### **9.1. Primary outcome:**

The primary outcome of sustained ROSC will be analyzed and calculated the odds ratio of ETI vs SGA. 95% confidence intervals will be used to quantify the treatment effect.

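### The trial randomises cluster-by-fortnight units, but the named analyses are in standard form patient-level methods with no cluster, period or cluster-period term, so the primary p-value and 95% CI do not match the design

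*Protocol*

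**What the plan says.** Section 4 of the protocol says that the trial "will use cluster randomization with periodic crossover". Section 4.5 gives the detail: "Four ALS teams will be divided into two randomization clusters. Each cluster is assigned to either ETI or SGA in a biweekly period". Periods are allotted as "three periods of ETI to two periods of SGA (3:2 ratio"). All eligible patients whom a cluster treats in a given fortnight therefore share one assignment.

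Section 9 names the methods: "The statistical analysis methods include descriptive analysis, T-test, Chi-squared test, logistic regression, and propensity score analysis". It adds odds ratios with 95% confidence intervals and a two-sided 0.05 significance rule. On the primary analysis, section 9.1 says: "The primary outcome of sustained ROSC will be analyzed and calculated the odds ratio of ETI vs SGA". Section 9.2 treats the secondary outcomes in the same way.

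The protocol nowhere mentions a random effect, GEE, a robust variance, an ICC, a design effect, or a term for cluster or period. The sample size in section 5 does not mention clustering either.

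**The concern.** Used in their ordinary form, the chi-squared test, the t-test and logistic regression take each patient as an independent observation. Here patients are assigned in blocks. If patients in the same cluster and fortnight have outcomes more alike than patients in different fortnights (for instance through season or caseload), each block carries less information than its head count suggests. The patient-level standard error is then too small, the CI too narrow, and the nominal 5% test rejects more often than 5% of the time. Propensity scores do not cure this, because they balance covariates and do not model correlation. The primary comparison and all secondary outcomes are affected.

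**Working it through.** **The plan's own figure.** The protocol gives no clustering figure to reproduce. It is worth asking whether 852 already contains an allowance. With 24.4% and 30.8%, 80% power and two-sided 0.05 (section 5), the pooled two-proportion formula for independent patients is

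n per arm = [1.96 × √(2 × 0.276 × 0.724) + 0.8416 × √(0.244 × 0.756 + 0.308 × 0.692)]² / 0.064² = 765, or 1,530 in total.

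So 852 as a total lies below the independent-patient number and holds no hidden design effect. That mismatch is a separate matter. Here 852 is used only as planned enrolment, which agrees with accrual: 300 per year × 34/12 = 850.

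**Inputs.** Two clusters and two-week periods (section 4.5); 34 months of enrolment (section 2); 852 patients (section 5). The ICC is assumed, because the protocol gives none.

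**Size of the randomised units.**
- Periods: 34 × 30.44 / 14 = 73.9.
- Cluster-periods: 2 × 73.9 = 147.8.
- Patients per cluster-period: 852 / 147.8 = 5.76.

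**Effect on the test.** Assume equal-sized cluster-periods and no correlation between periods. Then

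- design effect DE = 1 + (5.76 − 1) × ICC;
- required CI width relative to the patient-level CI = √DE;
- true size of the nominal 5% test = 2 × [1 − Φ(1.96 / √DE)].

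| Assumed ICC | DE | CI should be wider by | True size (formula) | True size (simulated) |
|---|---|---|---|---|
| 0 | 1.00 | 0% | 5.0% | 5.2% |
| 0.01 | 1.05 | 2% | 5.6% | 5.6% |
| 0.02 | 1.10 | 5% | 6.1% | 6.4% |
| 0.05 | 1.24 | 11% | 7.8% | 8.1% |
| 0.10 | 1.48 | 21% | 10.7% | 11.7% |

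The simulation applied the unadjusted two-proportion test to 148 cluster-periods with Poisson sizes of mean 5.76, three in five on ETI, and beta-binomial outcomes with mean 27.6% (20,000 trials per ICC). It runs a little above the formula at the higher ICCs because cluster-period sizes vary.

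**How plausible is each ICC?** On the probability scale, the SD of the true ROSC rate between cluster-periods is √(ICC × 0.276 × 0.724), where 0.276 is the mean of the two planning rates.
- ICC 0.01: 4.5 percentage points.
- ICC 0.02: 6.3 points.
- ICC 0.05: 10.0 points.
- ICC 0.10: 14.1 points.

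A fortnight-to-fortnight SD of 14 points around 27.6% is very large, so 0.10 is best read as an upper extreme.

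**The case against.** The strongest reply is that section 9 is silent rather than wrong. Its list is introduced by *include*, so it is open. Logistic regression can carry team, period and random-effect terms, and section 9.1 fixes only the effect measure. Model terms are often left to a statistical analysis plan, which was not available. This stands in part: a reader might infer that the protocol rules out any allowance for clustering, and it does not. But the protocol did not defer the matter. It names the methods and the significance rule, and someone who follows them as named gets an analysis that ignores the randomised unit.

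Second, the error may be small. This stands. At ICC 0.01 to 0.02 the inflation is about one percentage point or less. Because each cluster crosses over repeatedly, stable differences between the clusters largely cancel; if these dominated and were left out of the model, the standard error would be slightly too large instead. A design effect based on whole clusters of about 426 patients (852 / 2) would therefore greatly overstate the problem. If *biweekly* meant twice a week, cluster-periods would hold about 1.4 patients and the effect would be smaller still.

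Two stronger readings are tempting, and the document supports neither. One is that chance imbalance between few periods biases the comparison. There are about 74 periods with both devices recurring throughout, and nothing shows a material calendar imbalance. The other is that leaving registry covariates out of the primary estimate is an error. Section 9 lists logistic regression and propensity scores, section 9.1 does not exclude covariates, and an unadjusted primary estimate in a randomised trial is a choice about precision.

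**Conclusion.** The design and the named analysis do not match. The primary p-value and 95% CI are at their stated level only if outcomes are uncorrelated within cluster-periods, which the protocol neither claims nor supports. The mismatch is certain from the text; its size is not. Under an assumed cluster-period ICC of 0.01 to 0.02, the nominal 5% test has a true size of about 5.6% to 6.1% and the CI should be 2% to 5% wider. At 0.05 the size is about 7.8%, and at 0.10 about 10.7%. These figures rest on 852 patients over 34 months, two-week periods, roughly equal cluster-periods and no correlation between periods. A reader might infer that the false-positive rate is doubled; that needs the extreme end of the assumed range. The inflation is probably modest, but it bears on the primary inference and is cheap to remove.

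**What to change.** In section 9, make the primary analysis one prespecified model of sustained ROSC on assigned arm that accounts for the randomised unit. One suitable choice is logistic regression with:

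- fixed effects for cluster (or ALS team);
- a low-dimensional calendar-time term, such as quarter (about 11 or 12 levels over 34 months). One effect per fortnight would use about 73 parameters against roughly 235 expected events (852 × 0.276);
- a random intercept for cluster-period.

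Name one model rather than a menu, because a mixed model and GEE estimate different odds ratios (conditional and marginal). Do not use a robust variance clustered on the two clusters, since two units are too few for it to be reliable. Keep the chi-squared test as descriptive, and use the same model for the secondary outcomes. Adjustment for registry covariates is optional and not needed to correct this point.

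The cost is wording: no new data, patients or procedures. The CI may widen slightly if within-period correlation is present, and the odds ratio becomes conditional on the model terms, so it will not correspond exactly to the crude rates in section 5.

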### **9.1. Primary outcome:**

The primary outcome of sustained ROSC will be analyzed and calculated the odds ratio of ETI vs SGA. 95% confidence intervals will be used to quantify the treatment effect.

### **9.2. Secondary outcomes:**

Secondary outcomes include prehospital ROSC, survival to hospital discharge, and favorable neurological outcome will also be analyzed in a similar manner.

### 9.3. Subgroup analysis

Several subgroups will be analyzed to explore the association of different airway management devices, including patient's age, presenting shockable rhythm, arrest in a public location, arrest witnessed, and time of call to airway. The median will be chosen for analyzing for the call to airway time and the age of patients.

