## 3. Background

Resuscitation of out-of-hospital cardiac arrest (OHCA) patients is one of the most important issues in emergency medical service (EMS) care.

During cardiac arrest, the brain will be damaged to varying degrees due to low blood oxygen and circulation. High-quality cardiopulmonary resuscitation (CPR) is vital to

reduce the damage of cardiac arrest. Besides, effective ventilation is the basis to maintain the blood oxygenation in the brain, thereby reducing hypoxia and brain damage, and can increase the possibility of return of spontaneous circulation (ROSC) and the chance of neurologically intact survival. [1, 2]

For cardiac patients, the "chain of survival" emphasized early recognition, early CPR, early defibrillation, early advanced life support and post arrest care. There is no doubt about the benefits of early CPR and defibrillation. [3-5] While the prehospital airway management of OHCA patients remained controversial. The airway management in prehospital settings can be divided into basic and advanced techniques. The basic technique includes bag valve mask (BVM) and the advanced technique includes both supraglottic airway device (SGA) and endotracheal intubation (ETI).

The advantage of advanced airway management is to provide a definite and secure way of oxygen delivery in the first aid of sudden cardiac arrest patients. Compared to BVM, advanced airway management may further reduce the interruption during ambulance transport. Advanced care paramedics in Taiwan were authorized to perform either SGA or ETI in the prehospital setting. While ETI may have some pitfalls like esophageal intubation, CPR interruption and may further influence a patient's outcome. [6-10] Theoretically, the SGA can be established quickly, and some studies have also confirmed that the SGA is better than ETI in resuscitation and can reduce the interruption during CPR. [11] However, such inferences were questioned in the following studies. Compared with SGA, ETI achieved higher sustained ROSC (odds ratio [OR] 1.35; 95% confidence interval [CI] 1.19–1.54) according to the analysis from Cardiac Arrest Registry to Enhance Survival (CARES) registry. [12] A recent meta-analysis included 34,533 ETI patients and 41,116 SGA patients that revealed ETI had statistically significant higher odds of ROSC (OR 1.28, 95% CI 1.05-1.55) compared to SGA, while no RCT exists to compare these two airway interventions, resulting in an overall low quality of evidence. [13]

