#### **4.6. Exposure management**

##### **4.6.1. Intervention group**

The intervention arm of the trial is primary ETI in eligible patients according to inclusion criteria. The endotracheal tube will be inserted via direct laryngoscopy but

not video laryngoscopy. There is no additional training course for paramedics who are involved in this trial.

The confirmation of success ETI is mainly by end-tidal capnographic data and auscultation. Protocol-based single-attempt intubation is also applied.

If the first advanced airway attempt fails, rescue airway management including SGA insertion or BVM ventilation are allowed.

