#### **4.6.2. Control group**

The control arm of the trial is primary SGA insertion in eligible patients according to inclusion criteria. The SGA which is used in the trial is second-generation supraglottic airway device from Intersurgical (i.e., i-gel). There is no additional training course for paramedics who are involved in this trial. Misplacement of SGA is less common due to its design to create an anatomical seal of the pharyngeal, laryngeal and perilaryngeal structures. Protocol-based single-attempt SGA insertion is also applied. If the first advanced airway attempt fails, rescue airway management including ETI or BVM ventilation are allowed.

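### The call-to-airway subgroup in Section 9.3 is cut on a post-allocation time that the assigned device can change, so its within-stratum comparisons can be biased

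*Protocol*

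**What the plan says.** Protocol Section 9.3 names five subgroup factors: age, shockable presenting rhythm, public location, and finally "arrest witnessed, and time of call to airway". For the two continuous factors it sets the cut: "The median will be chosen for analyzing for the call to airway time and the age of patients". It does not say whether the median is pooled or taken within each arm.

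Section 7 defines the time as "call to airway time [defined as the gap between the call of the dispatch center and advanced airway insertion completion".

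Allocation is fixed earlier. Section 4.5 states: "Each cluster is assigned to either ETI or SGA in a biweekly period". The same section gives the baseline rates in the Taipei system: "the success rate of first attempt: 60% of ETI vs. 90% of SGA".

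A failed first attempt leads to rescue in both arms. For ETI (Section 4.6.1): "If the first advanced airway attempt fails, rescue airway management including SGA insertion or BVM ventilation are allowed". For SGA (Section 4.6.2): "If the first advanced airway attempt fails, rescue airway management including ETI or BVM ventilation are allowed".

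**The concern.** A subgroup comparison keeps the protection of randomisation only if the assigned treatment cannot affect which subgroup a patient falls into. Age, presenting rhythm, location and witness status are settled before any airway attempt. Call-to-airway time is not: its last component is the assigned procedure itself.

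If one device takes longer to place, or fails more often and needs a rescue airway, a cut on completion time sorts the two arms differently. Patients in the same stratum are then no longer comparable between arms. A patient rescued with BVM may have no completion time at all and so belong to neither stratum.

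At stake is the reading of this one subgroup. A difference produced by sorting could be reported as evidence on how the device effect varies with the timing of the airway.

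**Working it through.** The plan gives no figure for this analysis, so there is none to reproduce. The check has two parts: whether the device can move the variable, and how large the resulting bias could be.

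**1. Can the device move the variable?**

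- First-attempt failure, from Section 4.5: ETI 100% − 60% = 40%; SGA 100% − 90% = 10%.
- Rescue with the other device gives a later completion time. If a failed attempt costs *r* minutes, the mean shift between arms is (0.40 − 0.10) × *r*. That is 0.6 min for *r* = 2 and 1.2 min for *r* = 4. The values of *r* are assumed.
- Rescue with BVM may give no completion time. The protocol states no BVM-only rate, so this part is not quantified.

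**2. Why a pooled cut biases both strata under a null.** Let *U* be the time from call to airway attempt, unaffected by the device, and suppose ETI adds *d* minutes. With pooled median *m*, the early stratum holds ETI patients with *U* ≤ *m* − *d* and SGA patients with *U* ≤ *m*. The late stratum holds ETI patients with *U* > *m* − *d* and SGA patients with *U* > *m*. In both strata the ETI patients have the shorter *U*.

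**3. Hand calculation.** Assumptions, none from the protocol: *U* normal with mean 14 and SD 4 min; log-odds of ROSC fall 0.10 per minute of *U*; no device effect. Equal arms are used here because *m* is then 14 + *d*/2 by symmetry.

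With z = *d*/8, the gap in mean *U* between arms within either stratum is 4φ(z) × [1/Φ(−z) − 1/Φ(z)].

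For *d* = 2, z = 0.25:
- Share of each arm in the early half: ETI Φ(−0.25) = 40.1%, SGA Φ(0.25) = 59.9%.
- Gap: 4 × 0.3867 × (1/0.4013 − 1/0.5987) = 1.27 min.
- Log-odds: 0.10 × 1.27 = 0.127, an odds ratio of about 1.14.
- In points: the Section 5 rates weighted 3:2 give 0.6 × 30.8% + 0.4 × 24.4% = 28.2%. Then 0.282 × 0.718 × 0.127 = 0.026, or 2.6 points.

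The same formula gives a gap of 0.64 min (1.3 points) for *d* = 1 and 1.90 min (3.9 points) for *d* = 3.

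**4. Simulation.** Same assumptions, 60% ETI, 2,000,000 patients per scenario, overall ROSC equal in both arms:

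| Added ETI time | Early stratum, ETI − SGA | Late stratum, ETI − SGA |
|---|---|---|
| 1 min | +1.2 points | +1.1 points |
| 2 min | +2.6 points | +2.1 points |
| 3 min | +3.8 points | +3.3 points |

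At 3 minutes ETI makes up 46% of the early and 74% of the late stratum, instead of 60% of each.

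**5. Using the protocol's failure rates.** This variant has equal arms, 40% and 10% failure, 0 to 2 min of added ETI placement time, 0 to 4 min lost after a failure, and a slope of 0.05 or 0.10 per minute. Whenever the device changed the time, the null odds ratio was 1.02 to 1.17 in the early half and 1.02 to 1.22 in the late half. With failure delay alone (2 or 4 min), the ranges were 1.02 to 1.05 and 1.02 to 1.09. Splitting instead on a time that the device cannot change gave 0.99 to 1.01 in every scenario.

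**6. Against sampling error.** The planned 852 patients give 426 per stratum, about 256 ETI and 170 SGA. The standard error of a difference is √[0.282 × 0.718 × (1/256 + 1/170)] = 4.5 points. Across the strata it is about 4.2 to 4.7 points, so each bias in the table is below one standard error. The chance of a nominally significant stratum under the null is about 6% at 1 min, 8 to 9% at 2 min and 12 to 14% at 3 min, against a nominal 5%.

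**The case against.** The strongest reply is that this is one of five exploratory subgroups, that the bias is smaller than the noise, and that its size rests on assumed minutes and slopes. The limited scope and the assumed inputs stand. Exploratory status, however, deals with multiplicity and power. It does not make a contrast valid when assignment helps decide the stratum, and neither does analysing by intention to treat.

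Four stronger readings are tempting, and the documents do not support them.

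- *An ETI advantage would appear in both strata.* This does not follow. If failed attempts also mark patients with a worse prognosis, the sign can change. With 40% and 10% failure, 3 min lost after a failure, no other ETI delay and a log-odds penalty of 1 for difficult airways (all but the failure rates assumed), the null late stratum turns negative, at about −0.5 to −0.7 points.
- *The protocol itself says SGA is faster.* Section 3 says only "Theoretically, the SGA can be established quickly", and goes on to report that later studies questioned such inferences. It gives no placement time for either device. The support in the text is the difference in first-attempt success.
- *The median is pooled.* Section 9.3 does not say so. In the model above, arm-specific medians leave the bias within 0.2 points, but they would not turn the factor into a baseline variable.
- *BVM-only patients would be lost mainly from the ETI arm.* The protocol gives no BVM-only rate, and the handling of missing values may be in a statistical analysis plan that is not shown.

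**Conclusion.** The point holds as a limited one. Sections 7 and 9.3 together fix a subgroup on a post-allocation variable. Section 4.5's success rates and the rescue rules in Sections 4.6.1 and 4.6.2 show that the assigned device can change it. Within-stratum comparisons are therefore open to bias under a true null. This conclusion needs no assumed number.

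The size does. With a pooled median, 1 to 3 min of added ETI time and a slope of 0.10 per minute, the bias is about 1 to 4 percentage points per stratum. Other assumptions make it smaller or reverse its sign in one stratum. At the planned size it would usually be hidden by sampling error, so it is a reason not to interpret the subgroup and not a prediction of a false finding. The primary and secondary intention-to-treat analyses are untouched.

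**What to change.** In Section 9.3, replace call-to-airway time with response time as the subgroup factor. Section 7 already collects response time but does not define it. Add a definition under which it ends before any airway attempt, and state which unit's arrival it refers to, because Section 4.3 foresees participating paramedics arriving second on scene.

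Keep call-to-airway time as a process measure, reported descriptively by assigned arm, together with the number of patients who have no such time.

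The median split for age needs no change, since age is a baseline variable.

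The cost is a change of wording and one definition. No new variable has to be collected.
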